#### Economic data

Resource use will be collected on all aspects of intervention set-up and delivery. These include research staff, trainer, school staff and pupil time, expenses, travel, materials, venue hire costs and administration. Time burden for each component of intervention refinement and delivery will be logged by the research team, with respect to staff grade to determine cost. School staff and pupil time for peer nomination and intervention delivery will be recorded on proforma by research staff after consultation with school contacts. Intervention resources such as printed manuals, worksheets and equipment to facilitate the delivery of activities will be itemised, and the cost of hiring and transporting pupils to venues for the training will be recorded per school. Although the intervention has the potential to influence participants healthcare use long-term, we will not collect this information within the trial as we wish to minimise participant burden and do not believe the intervention is likely to influence healthcare use in the short term. Participant health-related quality of life will be measured using the EQ-5D-Y [44] and KIDSCREEN-10 [45] questionnaires.

### Participant appreciation

All participating schools will receive a £500 donation and a summary of project findings as appreciation for devoting time to the project. All consenting girls will receive a £10 ‘Love to Shop’ voucher after completing measures at each time point (£20 in total) to recognise their contribution to the project.

### Data analysis

Data will be entered electronically on a secure file store system and password protected. Data will be anonymised by assigning a unique identification number to each pupil.

#### Quantitative analysis

Trial outcome data will be reported in line with Consolidated Standards of Reporting Trials (CONSORT) guidance [46] and intervention elements will be described using the Template for Intervention Description and Replication (TIDieR) checklist [47]. The primary comparative analysis will be examined on an Intention-to-Treat (ITT) basis including all participants in randomisation without imputation for missing data. Multivariable mixed effects linear regression will be used to estimate differences in the primary outcome; objectively-assessed mean weekday minutes of MVPA, between intervention and control groups adjusting for baseline outcome score and randomisation variables. Secondary analysis will be similar and will adjust for further imbalanced variables between trial arms at baseline. Similar analyses will be repeated for secondary outcomes. A sensitivity analysis, using a suitable imputation method, will be conducted to assess the effect of missing data. *P*-values and 95% confidence intervals will be calculated. A small number of pre-specified subgroup analyses will be carried out to evaluate whether the intervention is differentially effective/cost-effective in different subgroups, such as by school-level socioeconomic position. The trial is not powered to detect effectiveness in subgroups, and this analysis will be treated as exploratory, presented using confidence intervals and interpreted with caution. Mediation analysis [48] will look at whether any intervention effect is mediated by the SDT constructs; autonomous motivation, perceived competence and peer norms for physical activity. No secondary per-protocol analysis is planned due to the informal nature of the intervention. However, if a school fails to deliver the intervention, a per-protocol analysis will be conducted based on whether the intervention training was delivered (yes/no). An additional sensitivity analysis of the intervention effect on the primary outcome will be performed if the school context audit shows a between arm difference of new school physical activity provision.

A public sector perspective will be taken in the economic analysis, including costs to Local Authorities and schools. To increase generalisability, national unit costs for trainer and teacher time will be used where available. Time spent by peer supporters receiving training will be reported, but the opportunity cost of pupil training and dissemination will not be included in the cost-effectiveness analysis. Cost per student within each school will be estimated by dividing the costs of the peer-supporter programme at that school by the total number of female students completing the primary outcome at T1. In line with the analysis of the primary outcome, imputation will be used as a sensitivity analysis. An incremental cost effectiveness ratio (ICER) will be determined by dividing the cost per pupil of the intervention by the difference in daily MVPA in the intervention and control arms. This will be repeated in pre-specified subgroup analysis (i.e. school level socioeconomic position). EQ-5D-Y and KIDSCREEN-10 responses will be used in secondary analyses to explore whether the intervention has any short-term impact on health-related quality of life. Currently, there is no value set for the EQ-5D-Y [49], so comparison between arms will be based on raw responses to each of the five items. A mapping algorithm will be used to estimate utility scores from the KIDSCREEN-10 and compare them between arms [50]. Health economics data will be reported as outlined in the Consolidated Health Economic Evaluation Reporting Standards (CHEERS) statement checklist [51].

If there is evidence that the intervention increases MVPA, we will explore whether existing epidemiological models can be used to extrapolate how sustained increases in MVPA might affect health outcomes and healthcare utilisation in adulthood. The identification of suitable models and a pre-specified effectiveness threshold at which extrapolation would be explored will be agreed with the Trial Steering Committee and detailed in a health economics analysis plan.

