### Allocation

School is the unit of allocation. Twenty schools will be randomly allocated after completion of baseline measures; ten intervention and ten control schools. Randomisation will be stratified by county (Avon, Devon and Wiltshire) and the England IMD score for the local super output area where the school is located to ensure balance within each stratum. The latter will be dichotomised as either above or below the median of sampled schools in the county. Random allocation will be performed (computer generated) by a member of the Bristol Randomised Trials Collaboration (BRTC: a UKCRC-registered Clinical Trials Unit) who will be blind to school identity and independent of the fieldwork team.

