### Sample size

The PLAN-A feasibility study [33] found a between-arm difference in mean weekday MVPA of 6.1 min with 95% confidence intervals between 1.4 to 10.8 min, suggesting that a target between-arm difference of 10 min of MVPA per weekday is achievable. Recognising that even smaller intervention effects on MVPA may also lead to meaningful differences in health at a population level, the sample size necessary to detect a range of differences in weekday MVPA (i.e., 10, 8 & 6 min) were calculated. Table 2 shows the power calculations where the following parameters are fixed: cluster size = 70 (informed by feasibility study [33]), intra class correlation (ICC) on weekday MVPA = 0.01 (informed by the feasibility study; T0 = <.0, T1 = .02, T2 = <.0001 and other studies [34, 35]), MVPA standard deviation = 20 min (based on feasibility study), coefficient of variation in cluster size of 0.22, 5% two-sided alpha and inflation to account for 30% of participants not providing primary outcome data. 12 schools and 800 pupils are required to detect a 10-min difference in MVPA with 90% power, however 20 schools and 1400 pupils would provide 90% power to detect a smaller 6-min difference in MVPA and ample power to detect an 8-min difference. Further accounting for correlation between baseline and follow-up measures of MVPA (ρ = 0.4) slightly reduces the number of schools required (last column, Table 2).

**Table 2 Tab2:** Sample size parameters

MVPA Difference (mins)	Power	N pupils (uninflated)	N pupils (inflated)	N Schools	N Schools when allowing for correlation between baseline and follow-up
10	90	560	800	12	10
10	80	420	600	10	10
8	90	700	1000	16	12
8	80	560	800	12	12
6	90	980	1400	20*	18
6	80	840	1200	18	16

*sample size used

Given the inherent uncertainty in many of these assumptions, we will recruit 22 schools (20 + 2 reserves) and randomise 20 schools and 1400 pupils to detect a 6-min difference in MVPA with at least 90% power.

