### Data collection

All primary and secondary measures will be taken at baseline (T0) and at 5–6 months post intervention (T1). At T0 only, participants will be asked the following descriptive variables: 1) home postcode to derive Index of Multiple Deprivation (IMD) estimates, 2) ethnicity, 3) family affluence [36], 4) whether they receive free school meals. The primary outcome - objective minutes of weekday MVPA, will be assessed using ActiGraph wGT3X+ and wGT3X-BT accelerometers. Participants will be asked to wear the devices for seven consecutive days at T0 and T1. Periods of ≥60 min of zero counts will be classified as ‘non-wear’ and removed. Participants will be included in the primary outcome analysis if they provide ≥2 valid weekdays of data (500 min of data between 06:00 and midnight). Evenson [37] cut points have been found to be the most accurate MVPA threshold for adolescents [38] and will be used., We will also estimate participants’ sedentary time using a cut-point of less than 100 counts per minute [37]. The following secondary outcomes will also be assessed using an ActiGraph accelerometer, mean weekend minutes of MVPA, and mean weekday and weekend minutes of sedentary time.

At both time points, participants will report their self-esteem using the Self-Description Questionnaire [32], and the three central constructs of SDT (autonomy [39], competence [40] and relatedness [39] need satisfaction) and self-determined physical activity motivation (Behavioural Regulation in Exercise Questionnaire-2, BREQ-2) [41] will be assessed using validated self-report questionnaires. Physical activity social support will also be assessed at T0 and T1 using two questions designed in the pilot study specifically for PLAN-A: 1) Has anyone in your year group talked with you recently about physical activity? (Yes, no I’m not sure) and 2) Did talking to anyone in your year help you to be more active? (Yes, no, I’m not sure, I didn’t speak to anyone).

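### The no-imputation, baseline-adjusted primary model leaves out girls who have a valid T1 outcome but no valid T0 accelerometry, so the analysed set is not all randomised participants and some precision is lost

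*Protocol article*

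**What the plan says.** The Quantitative analysis section sets three rules for the primary comparison. The first two come together: it will be "examined on an Intention-to-Treat (ITT) basis including all participants in randomisation without imputation for missing data". The third is the model, a multivariable mixed effects linear regression that estimates the difference "between intervention and control groups adjusting for baseline outcome score and randomisation variables". Imputation appears only outside the primary analysis: "A sensitivity analysis, using a suitable imputation method, will be conducted to assess the effect of missing data".

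Under Data collection, accelerometry is needed twice: "Participants will be asked to wear the devices for seven consecutive days at T0 and T1". The entry rule is "Participants will be included in the primary outcome analysis if they provide ≥2 valid weekdays of data", and no time point is attached to it. Under Allocation, baseline comes first: "Twenty schools will be randomly allocated after completion of baseline measures; ten intervention and ten control schools". The Sample size section includes "inflation to account for 30% of participants not providing primary outcome data" and has no separate line for missing baseline.

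**The concern.** Baseline MVPA comes from the same seven-day wear protocol as the outcome, so some girls will fail the wear criterion at T0 and meet it at T1. A regression with baseline MVPA as a covariate, and nothing filled in, has no row for such a girl. Her primary outcome is known, but it does not enter the primary estimate. The article describes no way of keeping her, and the imputation sensitivity analysis leaves the primary estimate as it is.

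Two things are at stake. The reported set would be labelled as everyone randomised when it consists of girls who complied on two occasions. Information on the primary outcome would also be given up, although a missing pre-randomisation covariate is simple to handle.

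**Working it through.** **Inputs.** All from the Sample size section: 70 girls per school, ICC 0.01, SD 20 min, coefficient of variation of cluster size 0.22, two-sided alpha 5%, 30% loss, difference 6 min, baseline to follow-up correlation 0.4, 20 schools, 1400 pupils. The share f of girls with a valid T1 outcome who lack a valid baseline is not in the article. I take f = 10% and 20% as an assumption and also show 0% and 30%.

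**The plan's own figure.** With design effect DE = 1 + ((1 + CV²)m − 1) × ICC, m = 70 gives 1 + (1.0484 × 70 − 1) × 0.01 = 1.724. Using a noncentral t with 2k − 2 degrees of freedom, the smallest number of schools per arm giving 90% power for 6 min is k = 7 (power 90.6%; k = 6 gives 84.6%). Then 2 × 7 × 70 = 980, 980/0.70 = 1400 and 1400/70 = 20 schools. All three figures in Table 2 are reproduced.

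**Who is dropped.** In a simulated set of 1400 girls with 30% of T1 values and an assumed 10% of T0 values missing at random, 977 had a T1 outcome. The baseline-adjusted complete-case model used 880 and dropped 97. With the baseline filled and an indicator added, all 977 were used. Only these row counts are used here, because the simulated model fits gave convergence warnings. The standard errors below are analytic.

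**Precision of the complete-case model.** Start from 980 girls with T1 data, or 49 per school, so that m = 49(1 − f). With 10 schools per arm:

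SE = 20 × √(1 − 0.4²) × √(2 × DE/(10m))

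- f = 0: m = 49, DE = 1.504, SE = 1.436
- f = 10%: m = 44.1, DE = 1.452, SE = 1.488, N = 882
- f = 20%: m = 39.2, DE = 1.401, SE = 1.550, N = 784

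**Precision with a missing indicator.** The right comparator is not 1.436, because that value needs an observed baseline for all 980 girls. A retained girl without baseline gets no variance reduction from it. The average residual variance is therefore 400 × (1 − 0.16 × (1 − f)), with m kept at 49:

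- f = 10%: variance 342.4, SE = √342.4 × √(2 × 1.504/490) = 1.450
- f = 20%: variance 348.8, SE = 1.463

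**Comparison.** 1.488/1.450 = 1.026 and 1.550/1.463 = 1.059. The complete-case SE is about 2.6% and 5.9% larger.

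**Power for 6 min, complete-case model, t with 18 df.**

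| f | Girls analysed | Ignoring baseline correlation | Correlation 0.4 |
|---|---|---|---|
| 0 | 980 | 95.1% | 97.7% |
| 10% | 882 | 93.7% | 96.8% |
| 20% | 784 | 91.8% | 95.5% |
| 30% | 686 | 89.2% | 93.7% |

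With the baseline correlation that the primary model uses, power is above 90% throughout.

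**The case against.** The strongest reply is that the exclusion is inferred. The article nowhere says that a girl needs valid data at both visits, the two-weekday rule has no time point, and handling of a missing covariate is often left to an analysis plan that is not shown. Part of this stands: the exclusion follows from the stated rules but is not written out. The article does fix a no-imputation rule without confining it to outcomes. An analysis plan that filled in baseline would depart from that wording, so the wording itself needs attention.

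Four stronger readings are tempting, and the document does not support them.

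- A reader might infer that the stated set and the stated model are irreconcilable. Girls without a T0 value can be kept with no imputation, by a mixed model that takes T0 and T1 jointly with a common baseline mean. What is true is narrower: the model as described, with baseline as a covariate, drops them.
- A reader might infer that the 30% inflation leaves this loss unbudgeted. The primary measure is taken at both visits, and the 30% can be read as total loss from the primary analysis. In that case 980 is already the complete-case number, and taking off a further 10-20% would count the loss twice.
- A reader might infer a biased arm comparison. Baseline precedes allocation, so excluding girls for missing baseline is exclusion on a pre-randomisation feature. It costs precision and some representativeness, and no bias is shown.
- A reader might infer an underpowered trial. The power figures rule that out over the assumed 10-20%.

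It is also fair to say that girls with no valid T1 outcome, planned at up to 30%, are the larger gap between the label and the analysed set. The planned imputation sensitivity analysis softens the problem too, though it does not alter the primary estimate.

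**Conclusion.** The point holds as a matter of accuracy and efficiency. Followed as written, the primary analysis excludes girls with an observed T1 outcome and no valid baseline, so it is not an analysis of everyone randomised. At an assumed 10-20% missing baseline among girls with T1 data, the standard error is about 2.6-5.9% larger than it need be (1.488 against 1.450 min, and 1.550 against 1.463 min). Power for 6 min remains above 90%.

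These sizes rest on the article's SD, ICC, cluster-size variation and correlation, on 980 girls having T1 data, and on an assumed rate of missing baseline. A lower rate shrinks the effect in proportion. The fix is worth making because it recovers observed primary outcomes without biasing the arm contrast and needs no new data.

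**What to change.** Change the primary-analysis wording in four places:

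1. Keep every girl with a valid T1 outcome. Where baseline MVPA is missing, fill it with a constant or the overall mean and add a missing-baseline indicator to the model. Alternatively, fit T0 and T1 jointly in a mixed model with a common baseline mean. Name one of these in advance.
2. Limit the no-imputation statement to outcome data.
3. State that the two-valid-weekday inclusion rule applies to T1.
4. Describe the set as all participants with a valid T1 outcome, analysed as randomised.

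The cost is a few sentences of text and a small departure from the simplest complete-case model. No additional data collection is needed. The change should be made before T1 data are analysed.

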
### Control group provision

All consenting Year 9 pupils in control schools will participate in T0 and T1 data collection, including peer nomination, however the 10 schools assigned to the control condition will not receive the intervention and will continue with normal practice. Results of the peer nomination will be made known to the control schools after T1 data collection.

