An audit will be conducted to assess school context. The tool, adapted and tested in the PLAN-A feasibility trial, will evaluate the quantity and quality of equipment/facilities in the school that promote physical activity among its pupils [42], as well as the schools’ physical activity policies and physical activity throughout the curriculum [43]. In addition, data on school size, pupil premium and termly after-school provision will be collected in order to account for school-specific factors that could explain changes in MVPA observed at T1. Any adverse events or unintended effects will be recorded and reported to the Chair of the Trial Steering Committee and the Chair of the ethics committee.

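### The contingent per-protocol analysis would compare a selected subset of intervention schools with all ten control schools; a complier-average analysis would avoid this

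*Protocol article*

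**What the plan says.** The primary analysis is stated clearly in the Quantitative analysis section: "The primary comparative analysis will be examined on an Intention-to-Treat (ITT) basis including all participants in randomisation without imputation for missing data". On per-protocol analysis the default is none: "No secondary per-protocol analysis is planned due to the informal nature of the intervention". One exception follows, for the case where a school does not deliver: "a per-protocol analysis will be conducted based on whether the intervention training was delivered (yes/no". The default and the exception do not contradict each other; the second is a contingency.

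The Control group provision section settles which schools can fail: "the 10 schools assigned to the control condition will not receive the intervention and will continue with normal practice". Table 1 places peer-supporter training after allocation, in ten schools.

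The Quantitative analysis section says that subgroup results will be treated as exploratory and read with caution. It attaches no such caution to the per-protocol estimate.

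**The concern.** Whether training was delivered is known only after randomisation, and only for one arm. Dropping the intervention schools that did not deliver removes a group of schools whose counterparts in the control arm cannot be identified and so stay in. If non-delivering schools would have had different MVPA anyway, the difference between the retained intervention schools and all ten controls mixes the effect of the intervention with that prior difference.

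What is at stake is the reading of a supplementary result. With ten schools per arm, one or two exclusions are enough to move it. It would be reported only when delivery had gone wrong, which is when readers will look for an estimate of the effect where the intervention was actually given.

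**Working it through.** **Inputs.** From the Sample size section: difference 6 min, SD 20 min, ICC 0.01, cluster size 70, coefficient of variation of cluster size 0.22, two-sided alpha 5%, 30% without primary outcome data. From Allocation: ten schools per arm. Assumed here: non-delivering intervention schools are dropped and all controls kept (the usual meaning of per-protocol), and failing schools differ from the rest by 1 to 2 between-school SDs.

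**The plan's own figure.** Design effect = 1 + ((1 + 0.22²) × 70 − 1) × 0.01 = 1.724. With 7 schools of 70 per arm, SE = 20 × √1.724 × √(2/490) = 1.678 min, and power for 6 min (noncentral t, 12 df) is 90.6%. With 6 per arm it is 84.6%. So 14 × 70 = 980 pupils; 980/0.7 = 1400; 1400/70 = 20 schools. This agrees with Table 2, so the planning inputs can be used as they stand.

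**Between-school SD.** √0.01 × 20 = 2.0 min.

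**Bias of the per-protocol estimate.** Let p be the share of schools that would fail to deliver, g the untreated mean of delivering schools minus that of failing schools, and τ the effect where training is delivered. By randomisation the control arm contains, in expectation, the same share p of would-be failing schools, so its mean lies p × g below that of the would-be delivering schools. Retained intervention schools minus all controls therefore estimates τ + p × g. The shift is p × g:

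| Failing schools | g = 2 min | g = 4 min |
|---|---|---|
| 1 of 10 | 0.2 min (3.3% of 6) | 0.4 min (6.7%) |
| 2 of 10 | 0.4 min (6.7%) | 0.8 min (13.3%) |

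If g is negative, the sign reverses.

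**A bound on selection.** If the two schools with the lowest underlying means are the two that fail, normal order statistics for ten schools give an expected gap to the other eight of about 1.59 SD, or 1.59 × 2 = 3.2 min. The expected shift is 0.2 × 3.2 = 0.64 min, about 11% of 6. A gap of 4 min with two failing schools is therefore beyond what perfect selection gives on average.

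**Loss of power is not the issue.** With 49 analysed girls per school (0.7 × 70), power for 6 min is 95.1% with no school dropped, 93.9% with one and 92.3% with two.

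**The alternative.** If non-delivering schools get no effect and schools are of equal size, ITT = (1 − p) × τ, so the complier-average estimate is ITT/(1 − p). An ITT estimate of 6.0 min becomes 6/0.9 = 6.7 with one failing school and 6/0.8 = 7.5 with two. The interval scales by the same factor: 1/0.9 = 1.11 and 1/0.8 = 1.25. All 20 schools stay in.

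**The case against.** The analysis is contingent, openly named per-protocol, and cannot displace the ITT result. It may never be run. That stands, and it makes the point minor.

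A reader might infer that the bias favours the intervention, because schools that fail are the less engaged ones. The documents do not say so. Training is given by freelance trainers at sites away from school, so a failure could lie with a trainer or a venue and have little to do with the school. The possibility of bias stands; its direction is not established.

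The sizes above are before adjustment for baseline MVPA, which the primary model includes; the same adjustment here would generally reduce the shift. The ICC is also a planning value, and the feasibility estimates were near zero at two of three time points. Both are fair, and they mean that the figures show scale and are not forecasts.

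The complier-average estimate is not free of assumptions. It requires that allocation affects MVPA only through delivered training. Training comprises two days plus a later top-up day, so a school that gave part of it but is coded as not delivering could still show some effect. Against that, peer nomination takes place in both arms and the ten-week intervention follows the training, so the assumption is credible here.

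A reader might extend the criticism to the second contingent analysis, which runs "if the school context audit shows a between arm difference of new school physical activity provision", and infer that it adjusts away part of the effect. The text gives only that trigger. It names no covariate, exclusion or model, and a trigger alone does not condition the estimate on later events. The Process evaluation section says that school-level data are collected "in order to account for school-specific factors that could explain changes in MVPA observed at T1", which hints at adjustment but fixes no method. That detail commonly sits in an analysis plan, so the criticism is not supported.

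**Conclusion.** The point holds for the per-protocol analysis only, as a minor improvement. As written, it yields a non-randomised supplementary estimate that can be biased in either direction. Under the plan's ICC and SD, the shift is about 0.2 to 0.4 min with one failing school and 0.4 to 0.8 min with two, and about 0.64 min on average if the two lowest schools are the ones that fail. These figures rest on the assumed 2 to 4 min gap (except the 0.64), on exclusion of non-delivering schools with all controls kept, and on no baseline adjustment.

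It would be too strong to conclude that the randomised comparison of the trial is broken: the ITT analysis includes everyone randomised, and no figure in the protocol depends on this contingency.

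**What to change.** Replace the contingent per-protocol analysis with a complier-average causal effect analysis, run only if a school fails to deliver. Allocation is the instrument and training delivered (yes/no) at school level is the exposure. Adjust for baseline MVPA and the randomisation variables, retain clustering by school, and label the result as supportive of the ITT estimate. Define before follow-up data are seen what counts as delivered, including how a school that completed only part of the training is coded.

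The cost is a sentence or two of wording and one instrumental-variable model, using delivery data that the yes/no definition already requires. The statistical price is the exclusion assumption and, with equal school sizes, an interval about 11% wider than the ITT interval with one failing school and about 25% wider with two.

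If the team prefers to keep the per-protocol analysis, the least it should do is describe the estimate as non-randomised and supportive, with the caution already given to subgroups.
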